# Statistical Analysis Plan (SAP)

[figure not shown]

## Appendix L: CTCAE v5.0 laboratory grades

| Lab parameter              | Units              | Grade 1                                                                 | Grade 2         | Grade 3          | Grade 4    |
|----------------------------|--------------------|-------------------------------------------------------------------------|-----------------|------------------|------------|
| sodium                     | mmol/L             | low
130 - < LLN                                                      | 125-129         | 120-124          | <120       |
| potassium                  | high               | >ULN - 150                                                              | >150 - 155      | > 155-160        | > 160      |
|                            | low                | 3.0 - < LLN                                                             | 3.0 - < LLN     | 2.5 - < 3.0      | < 2.5      |
| Alanine aminotransferase   | High               | > ULN - 5.5                                                             | > 5.5 - 6.0     | > 6.0 - 7.0      | > 7.0      |
|                            | High               | >ULN - 3* ULN if baseline normal; >1.5 - 3*ULN if baseline abnormal     | > 3 - 5*ULN     | > 5 - 20*ULN     | > 20*ULN   |
| Alkaline phosphatase       | U/L                | >ULN - 2.5* ULN if baseline normal; >2.0 - 2.5*ULN if baseline abnormal | > 2.5 - 5*ULN   | > 5 - 20*ULN     | > 20*ULN   |
| Aspartate aminotransferase | U/L                | >ULN - 3* ULN if baseline normal; >1.5 - 3*ULN if baseline abnormal     | > 3 - 5*ULN     | > 5 - 20*ULN     | > 20*ULN   |
| Total bilirubin            | umol/L             | High
>ULN - 1.5* ULN                                                 | > 1.5 - 3*ULN   | > 3 - 10*ULN     | > 10*ULN   |
| Serum creatinine           | umol/L             | High
> ULN - 1.5* ULN                                                | > 1.5 - 3.0*ULN | > 3.0 - 6.0 ULN  | > 6.0*ULN  |
| Creatine kinase            | U/L                | High
> ULN - 2.5* ULN                                                | > 2.5 - 5.0*ULN | > 5.0 - 10.0 ULN | > 10.0*ULN |
| Albumin                    | g/L                | low
30 - < LLN                                                       | 20 - <30        | < 20             |            |
| Calcium                    | mmol/L             | Low
2.0 - < LLN                                                      | 1.75 - < 2.0    | 1.5 - < 1.75     | < 1.5      |
| GGT                        | High               | >ULN - 2.9                                                              | >2.9 - 3.1      | >3.1 - 3.4       | >3.4       |
|                            | High               | >ULN - 2.5*ULN if baseline normal; >2.0 - 2.5*ULN if baseline abnormal  | >2.5 - 5.0*ULN  | >5.0-20.0*ULN    | >20.0*ULN  |
| Hemoglobin                 | g/L                | low
100 - <LLN                                                       | 80 - < 100      | < 80             |            |
| Neutrophils                | High               | Increase >0-20                                                          | Increase >20-40 | Increase >40     |            |
|                            | Low                | 1.5 - < LLN                                                             | 1.0 - <1.5      | 0.5 - <1.0       | <0.5       |
| Lymphocytes                | Low                | 0.8 - <LLN                                                              | 0.5 - <0.8      | 0.2 - <0.5       | <0.2       |
|                            | High               | -                                                                       | >4-20           | >20              | -          |
| Platelets                  | 10  /L | Low
75 - <LLN                                                        | 50 - <75        | 25 - <50         | <25        |

[figure not shown]

[figure not shown]

[figure not shown]

Supplement: Supplementary file 1 — Supplementary Note (Protocol and Statistical Analysis Plan (SAP)). [file 41591_2025_3971_MOESM1_ESM.pdf]

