| Scheduled Week                                                           | --                |        |    |    |    |    |    |                 |    |        |     |     |     |                     | 30                      |                  |
| Scheduled Day                                                            | -28 Day to -1 Day | 1      | 15 | 29 | 43 | 57 | 71 | 85              | 99 | 113    | 127 | 141 | 155 | 169                 | 8 weeks after last dose |                  |
| Visit Window (days)                                                      | --                | --     | ±2 | ±2 | ±2 | ±2 | ±2 | ±2              | ±2 | ±2     | ±2  | ±2  | ±2  | ±2                  | ±7                      |                  |
| RF, CCP antibodies                                                       | X                 |        |    |    |    |    |    |                 |    |        |     |     |     |                     |                         |                  |
| FSH testing l                                                 | X                 |        |    |    |    |    |    |                 |    |        |     |     |     |                     |                         |                  |
| Serum pregnancy testing m                                     | X                 |        |    |    |    |    |    |                 |    |        |     |     |     |                     |                         |                  |
| Urine pregnancy testing m                                     |                   | X      |    | X  |    | X  |    | X               |    | X      |     | X   |     | X                   |                         |                  |
| Urinalysis a                                                  | X                 | X      |    | X  |    |    |    | X               |    | X      |     |     |     | X                   | X                       |                  |
| Safety laboratory testing (hematology and chemistry)                     | X                 | X      |    | X  |    | X  |    | X               |    | X      |     | X   |     | X                   | X                       |                  |
| ESR                                                                      | X                 | X      |    | X  |    | X  |    | X               |    | X      |     | X   |     | X                   | X                       |                  |

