| Compliance                                      | Compliance (%) = 100 * (number of visits with treatment received/ number of visits with treatment planned) during the participant's participation in the study.
Compliance is calculated for Part A, Part B and Part A+B using the number of visits with treatment received during the respective Part and planned number in each Part also. |
| Baseline Derivations                     |                                                                                                                                                                                                                                                                                                                                                 |
| Baseline definition                             | Baseline will be defined as the last non-missing measurement prior to first dose of study medication in Part A For baseline characteristics table, if a subject is randomized and not treated then the latest record will be defined as the baseline.                                                                                           |
| Baseline definition for ADA                     | The last sample prior to the first dose of sonelokimab                                                                                                                                                                                                                                                                                          |

|                                                                                                        |                                                          |
|--------------------------------------------------------------------------------------------------------|----------------------------------------------------------|
| Change from baseline                                                                                   | The value at each time point minus the value at baseline |
| Other Derivations                                                                               |                                                          |
| Definition for the derived efficacy parameters are given in the respective efficacy analysis sections. |                                                          |

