### 8.9.2 Clinical Laboratory Evaluations

All central laboratory (hematology, biochemistry, urinalysis) parameters will be collected as described in [Appendix I](#).

Observed and change from baseline values for clinical laboratory parameters will be summarized using descriptive statistics by treatment group and visit separately for Part A and Part B. Shift from baseline to each scheduled assessment and the worst post treatment value according to normal ranges criteria will be presented. Shift from baseline to each scheduled assessment and the worst post treatment value according to CTCAEv5.0 criteria will also be presented. CTCAEv5.0 criteria are described in [Appendix L](#). Participants meeting any grade 3 criteria will also be listed.

In addition, the number and percentage of participants meeting the criteria for normal ranges in laboratory parameters will be summarized by treatment group separately for Part A and Part B.

Laboratory results together with the normal ranges will be listed, flagging values that are below or above the normal range. Serum/urine pregnancy tests assessments will be listed only.

Boxplots of the observed and change from baseline values for all clinical laboratory parameters will be presented by treatment group and visit for Part A and Part B. Reference lines for the normal ranges, that consistent across all participants being presented, will be displayed.

For participants with an AE of grade 3 or higher the hematology and chemistry lab parameters for that participant will be presented in a panel plot with a panel for each lab parameter. The x-axis will be the study week and the y-axis will be the absolute lab value.

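### Two laboratory grading rules in SAP Appendix L do not give one usable grade per value: low potassium has the same interval under Grades 1 and 2, and the haemoglobin-high rule has no ULN reference

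*Combined protocol and SAP*

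**What the plan says.** SAP Section 8.9.2 plans this output: "Shift from baseline to each scheduled assessment and the worst post treatment value according to CTCAEv5.0 criteria will also be presented". It adds that "CTCAEv5.0 criteria are described in" Appendix L, and that "Participants meeting any grade 3 criteria will also be listed". Appendix L is therefore the rule the programmer will code.

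In Appendix L, the low-potassium limits are 3.0 to below LLN for Grade 1, the same interval for Grade 2, 2.5 to below 3.0 for Grade 3, and below 2.5 for Grade 4. Nothing is printed to separate the first two.

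The haemoglobin-high cells are "Increase >0-20" for Grade 1, "Increase >20-40" for Grade 2, and an increase above 40 for Grade 3. None says what the increase is measured from or whether the value must be above ULN. The nearest definition elsewhere is change from baseline in SAP Section 7.1: "The value at each time point minus the value at baseline".

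**The concern.** A shift table needs exactly one grade for each value. The potassium row gives two grades for one interval, so the result would depend on the order in which the program tests its conditions. The haemoglobin row can be coded, but read literally it grades ordinary within-person variation and recovery from a low baseline as high-haemoglobin abnormalities.

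Clinically relevant laboratory abnormalities are a stated safety endpoint (SAP Section 4.5). A haemoglobin-high table in which most participants in every arm are graded by chance tells the reader little, and the Grade 3 listing could name participants whose haemoglobin has only returned towards normal.

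**Working it through.** The plan gives no figure to reproduce, so the check is to code the cells as written and apply them.

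**Which row is haemoglobin.** In the text available here the labels in Appendix L are displaced by one row: high limits on a sodium scale (150 to 160) stand beside potassium, and those on a calcium scale (2.9 to 3.4) beside GGT. The increase row stands beside neutrophils, directly after the haemoglobin low limits in g/L, and limits on a neutrophil scale (1.5, 1.0, 0.5) come in the next row. I read the increase row as haemoglobin in g/L. That is an inference.

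**Potassium.** LLN is not given; I assume 3.3, 3.5 or 3.6 mmol/L.

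| Value (mmol/L) | Grades met, LLN 3.3 | LLN 3.5 | LLN 3.6 |
|---|---|---|---|
| 2.4 | 4 | 4 | 4 |
| 2.9 | 3 | 3 | 3 |
| 3.0 | 1 and 2 | 1 and 2 | 1 and 2 |
| 3.2 | 1 and 2 | 1 and 2 | 1 and 2 |
| 3.4 | none | 1 and 2 | 1 and 2 |

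Whatever the LLN, every value from 3.0 to below it meets both grades. Values below 3.0 meet only one.

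**Haemoglobin, single cases.** Let d = visit value minus baseline. As written: 0 < d ≤ 20 is Grade 1, 20 < d ≤ 40 is Grade 2, d > 40 is Grade 3. The lowest value allowed at screening is 85 g/L (protocol Section 9.1.2, criterion 26g). ULN is not given; I assume 155, 165 or 175 g/L.

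| Baseline to visit (g/L) | d | Grade as written | Grade if counted above ULN (all three ULNs) |
|---|---|---|---|
| 130 to 131 | 1 | 1 | none |
| 130 to 150 | 20 | 1 | none |
| 110 to 131 | 21 | 2 | none |
| 85 to 126 | 41 | 3, listed | none |

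**Haemoglobin, chance of a graded worst value in Part A.** Protocol Table 1 schedules "Safety laboratory testing (hematology and chemistry") at Weeks 4, 8 and 12, so k = 3. If nothing changes and the baseline and k later values are exchangeable without ties, baseline is the largest of the k + 1 with probability 1/(k + 1). Hence

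P(at least one later value above baseline) = k/(k + 1) = 3/4 = 75%.

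Rounding to whole g/L creates ties and lowers this a little. A simulation used 400,000 participants, mean 140 g/L, between-person SD 12 g/L and no effect (all assumed):

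| Within-person SD (g/L) | Any grade | Grade 1 | Grade 2 or 3 | Any grade if ULN-anchored (ULN 155 / 165 / 175) |
|---|---|---|---|---|
| 3 | 70.3% | 70.3% | 0.0% | 14.3% / 3.0% / 0.4% |
| 5 | 72.3% | 71.8% | 0.5% | 18.4% / 4.5% / 0.6% |
| 8 | 73.3% | 64.8% | 8.5% | 25.8% / 8.2% / 1.7% |

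**Comparison with the rest of the table.** Grade 1 for high values is tied to ULN for sodium, potassium, ALT, AST, alkaline phosphatase, total bilirubin, creatinine, creatine kinase, calcium and GGT. High lymphocytes is the one other exception, with a fixed limit.

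**The case against.** The strongest reply is that the table is visibly damaged in these rows. The haemoglobin label is inferred, and the repeated potassium interval could be a merged cell read twice or a cell that lost a qualifier. That stands as a reason to check the source PDF. It does not dispose of the point: the displacement affects labels and units, the grade cells otherwise run in order, and no other section supplies the missing distinction or reference.

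A second reply is that the High label already implies a value out of range, and that Appendix L and Section 8.9.2 name CTCAE v5.0 as the standard. A careful programmer might code it that way. But the increase cells do not say so, whereas most other high rows name ULN explicitly.

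Four stronger readings are tempting, and the documents do not support them.

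- A reader might infer that potassium values will be misgraded, or Grade 2 counts inflated. The grade is undetermined, not shown to be wrong, and no number of affected participants can be derived.
- A reader might infer that Appendix L departs from CTCAE v5.0, or that symptoms should separate potassium Grades 1 and 2. The CTCAE text is not in the documents, so neither can be judged here.
- A reader might extend the chance calculation to six visits through Week 24 (6/7). Section 8.9.2 presents laboratory results separately for Part A and Part B, and Section 8.1 limits Part A+B tables to adverse events, so no clearly planned laboratory table matches that figure.
- A reader might infer that a real haemoglobin shift would be hidden. Section 8.9.2 also plans normal-range shift tables, observed and change-from-baseline summaries, boxplots and flagged listings, where it would still show.

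**Conclusion.** The concern holds as a defect in two grading rules. Low potassium from 3.0 to below LLN has no determined grade. The haemoglobin-high rule, read as change from baseline, grades rises within the normal range: about 3/4 of participants by chance at the worst Part A value, mostly as Grade 1, with some rises reaching Grade 2 or the Grade 3 listing.

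This rests on the haemoglobin reading of the row, on an increase meaning change from baseline with no out-of-range condition, and on exchangeable values with no true change. The percentages after rounding also depend on the assumed SDs.

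The consequence is minor. It is confined to the descriptive CTCAE shift, worst-value and Grade 3 listing outputs. The normal-range shift tables, the low-haemoglobin grades, potassium Grades 3 and 4, and all efficacy results are unaffected.

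**What to change.** First compare both rows with the source PDF. If they stand as read here:

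- **Haemoglobin high (three cells).** Grade only values above ULN, as most other high rows do, and state what the increase is measured from.
- **Low potassium (Grade 1 and Grade 2 cells).** Make the two cells mutually exclusive so that each laboratory value maps to one grade, with the sponsor stating what separates them.

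The cost is a few cells in one appendix and the matching lines of the grading program. No new data or change in trial conduct is needed.
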